- Vaccines that do not contain live viruses or bacteria (e.g., flu, Pneumovax , tetanus)

These vaccines may not be effective when administered in the presence of therapeutic circulating levels of Efalizumab.

Instructions to Subjects

The following instructions should be given to subjects:

- All medications being used must be reported to the investigator.
- Donations of blood or blood products are not allowed during the study and for at least 3 months following the last injection of study drug.
- Treatment with immunotherapies such as killed virus vaccines, toxins, and allergy desensitization may not be effective during therapy with Efalizumab.

Subjects who require such vaccines (e.g., tetanus toxin booster, influenza vaccine) should be encouraged to schedule these at least 14 days prior to Day 0 or at least 3 months following the last injection of study drug.

- Vaccines that contain live organisms (e.g., BCG, measles) should not be administered in the presence of study drug (Day–14 through Day 84).
- If any new drugs are prescribed by any health care provider during a subject’s participation in the study, the subject should notify the prescribing physician of his or her participation in this study and notify the study staff of the new medications.
- Tanning beds, booths, or home UV light sources are prohibited from
  Day –14 through Day 84.
- If the subject experiences acute adverse events, such as headache, fever, chills, myalgia, nausea, or vomiting 12–48 hours following SC injection of study drug, the subject may be provided with the recommended therapy. Headache, fever, chills, or myalgia may be treated with acetaminophen or other nonprescription analgesic, if needed. Nausea or vomiting may be treated with an approved anti-emetic as needed. If the symptoms are severe, the subject should contact the investigator.
- Allergic reactions or hypersensitivity reactions such as hives or throat tightness should be reported immediately to the investigator. The subject should also seek immediate medical attention.
- Signs and symptoms of an infection should be promptly reported to the investigator.

See appendix G for a detailed patient information sheet taken from the drug label.

These instructions apply through Day 84. Subjects will receive a written instruction sheet on Day 0.

Compliance with Laws and Regulations

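### The subject instructions, including the duty to report allergic reactions and infections and the bar on live vaccines, stop at Day 84, although efalizumab is dosed for 24 weeks and self-injected from week 13

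*Protocol*

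**What the plan says.** Under Instructions to Subjects, the protocol lists what each subject must be told and ends with "These instructions apply through Day 84". A written sheet is handed out on Day 0.

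The items differ in how they state their duration:

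- **No end date of their own.** "Allergic reactions or hypersensitivity reactions such as hives or throat tightness should be reported immediately to the investigator". Also: "Signs and symptoms of an infection should be promptly reported to the investigator". For acute symptoms after an injection: "If the symptoms are severe, the subject should contact the investigator".
- **Longer than Day 84.** "Donations of blood or blood products are not allowed during the study and for at least 3 months following the last injection". New prescriptions are to be notified if they arise "during a subject’s participation in the study". Non-live vaccines are best given well before Day 0 or at least 3 months after the last injection.
- **Day 84 in the item itself.** "Vaccines that contain live organisms (e.g., BCG, measles) should not be administered in the presence of study drug (Day–14 through Day 84"; the UV item likewise runs from Day –14 through Day 84.

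Elsewhere, Dosage, Administration, and Storage sets 24 weekly doses, given by staff for the first 12 weeks and self-injected in weeks 13-24. The Day 84 visit includes teaching on administration and lists no clinic dose. Excluded Therapies has a heading that covers the whole of treatment, but each of the four classes beneath it ends at Day 84. Criteria for Discontinuation of Treatment lists a live virus or bacteria vaccine with no end date.

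**The concern.** The instructions end at the hand-over from clinic to home dosing. Up to then, a staff member sees the patient weekly and gives the injection. Afterwards no staff member is present at dosing, and between visits the patient's own call is the quickest route to the investigator. The protocol body stops asking for that call at this point, for events that it wants reported at once or promptly.

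These events are not remote possibilities for this drug. The safety reports listed under Clinical Experience with Efalizumab include laryngospasm, an allergic drug reaction, Legionella pneumonia and abscesses.

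The live-vaccine item raises a separate problem. A patient who follows the dates given, and has a live vaccine in week 16, obeys the instruction. The same patient then meets a criterion for stopping treatment while still on drug.

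**Working it through.** The protocol gives no figure for this point, so the check compares the stated limit with the dosing schedule and then sets the texts side by side.

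**Inputs**
- Limit: Day 84 (Instructions to Subjects).
- Doses: 24, weekly, the first on Day 0 (Dosage, Administration, and Storage; Day 0 visit list).
- Clinic injections for the first 12 weeks, self-injection in weeks 13-24 (same section).
- Last visit: Day 168, Week 24 (visit list for Days 112, 140 and 168).

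**Dose days.** With no dose missed, dose k falls on Day 7 × (k − 1):
- dose 12: 7 × 11 = Day 77
- dose 13: 7 × 12 = Day 84
- dose 24: 7 × 23 = Day 161

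**Doses after the limit**
- If dose 13 is taken on Day 84, the limit covers 13 doses: 24 − 13 = 11 remain, and 11/24 = 45.8%.
- If dose 13 is taken later, it covers 12: 24 − 12 = 12 remain, and 12/24 = 50.0%.

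**Time after the limit**
- To the last scheduled dose: 161 − 84 = 77 days.
- To the Week 24 visit: 168 − 84 = 84 days.

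**Texts side by side**

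| Item | Instructions to Subjects | Elsewhere in the protocol |
| --- | --- | --- |
| Allergic reactions, infection | No own date, so the closing sentence supplies Day 84 | Drug continues to Day 161 |
| Live vaccines | Day –14 through Day 84, described as the time when drug is present | Drug continues to Day 161; a live vaccine is a stopping criterion with no end date |
| Four excluded classes | Not applicable | Excluded Therapies: the heading covers all of treatment, each line ends at Day 84 |

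Two details settle the live-vaccine row. First, the stopping criteria for systemic psoriasis treatment, immunosuppressants and experimental drugs apply only to excluded treatments, so they could be read as ending with the exclusion dates. The live-vaccine criterion has no such qualifier. Second, treatment cannot be taken to end at Day 84, because the visits on Days 112, 140 and 168 are listed under Assessments during Treatment.

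The item on severe acute symptoms is also cut off, but this matters less. The protocol reports that such events exceeded placebo only after the first two injections.

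**The case against.** **Patients may be told the right thing elsewhere.** The sentence just before the limit refers to Appendix G, a patient sheet taken from the drug label, and Procedures to Minimize Risks says that patients receive it. It was not available for this review. It may repeat the reporting advice with no end date. This stands as a limit on the practical consequence, but it does not correct the protocol body. If the closing sentence is meant to cover Appendix G too, the label advice would itself be limited to Day 84.

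**Adverse events are still collected.** The Abstract has patients seen every other week in the second 12 weeks, evaluated for adverse events at each visit, with monthly safety laboratory tests. The visit list has Weeks 16, 20 and 24. The adverse-event reporting rules have no Day 84 limit. A reader might infer that hypersensitivity or infection events would be lost after Day 84; the documents do not support that. What remains is that visits two weeks apart, or four on the visit list (112 − 84 = 28 days), do not replace an immediate call.

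**The list does not strictly contradict itself.** A reader might infer that the blood-donation, non-live-vaccine and new-prescription items clash outright with the closing sentence. On an ordinary reading, an item's own longer period governs over a general closing line. This is loose drafting, not two incompatible orders.

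**The UV limit is defensible.** A reader might set it against the inclusion criterion, which asks for avoidance throughout the study. That criterion concerns willingness at entry, whereas the instruction governs conduct, and Day 84 is the primary analysis time. Strict control to that day can be a deliberate choice.

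**The vaccine item gives its own reason.** A patient still injecting is plainly exposed to drug, so a careful reader would not rely on the date. But the item equates exposure with a period ending at Day 84, and a patient is likelier to follow a date than a rationale.

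**Conclusion.** The closing sentence is wrong for a 24-week treatment. As written in the protocol body, the duties to report allergic reactions and infections end as home dosing begins, and live vaccines are barred only to Day 84 although drug is scheduled to Day 161. The mismatch covers 11 or 12 of 24 doses and 77 days to the last scheduled dose, assuming weekly dosing from Day 0 with none missed. These figures give the extent of the mismatch, not a measure of harm. The number of patients or events affected cannot be derived from the documents.

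The textual error is certain. Its practical effect is not, because of the continued visits and the unseen Appendix G. The primary outcome at Day 84 is untouched, and sample size and error rates are not involved. It should be corrected because, followed literally, it is a wrong safety rule and costs almost nothing to change.

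**What to change.** 1. Replace the closing sentence with: *These instructions apply throughout study drug treatment (through the Week 24 visit), and longer where an item states a longer period.*
2. This does not correct items that carry their own date. Change the live-vaccine end date to the end of treatment, both in Instructions to Subjects and in Excluded Therapies.
3. Bring the other three Day 84 end dates in Excluded Therapies (systemic psoriasis therapy, immunosuppressants, experimental drugs) into line with the heading above them. Editing only the vaccine line would leave these in conflict with it.
4. Re-issue the corrected sheet at the Day 84 visit, where self-administration is already taught, and check that Appendix G carries no Day 84 limit.

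Aligning the UV item with the inclusion criterion is optional. There is a modest case for it, since PASI is a secondary outcome out to week 24.

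The cost is six line edits (one closing sentence, two live-vaccine lines, three other exclusion lines) and one re-issued sheet at an existing visit. No additional visit, staff or procedure is needed.

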**12. Recruitment and Consent Procedures:**

Subjects are recruited from the patient populations of The Rockefeller University, the New York Hospital, and general communities in which these institutions are located. Eligible patients selected will be of either sex in approximately equal numbers. As in all our protocols, individuals will be selected without regard to race or ethnicity.

13. Risks and Alternative Methods:

The risks to treatment with Efalizumab are outlined in a previous section. As with any medication, there are always unknown risks. Another theoretical risk is a possible allergic reaction. There are minor risks to skin biopsy (infection, bleeding, a small scar) and to phlebotomy from peripheral veins (bleeding, bruising). The risks of Efalizumab treatment in pregnancy or during lactiation are unknown.

Other treatments are available for the treatment of psoriasis, but each alternative (phototherapy, photochemotherapy, methotrexate, etretinate) have a therapeutic index, which precludes long-term treatment. In contrast, Efalizumab offers the potential of a treatment with reduced toxicity and with highly selective effects on cells mediating this disease.

**14. Data and Safety Monitoring Plan:**

This project entails moderate risk to subjects. Monitoring will be conducted a) by the Principal Investigator (PI) in consultation with the Clinical Research Safety Officer of the ACCTS and b) by the PI and the Rockefeller University Institutional Review Board (IRB), through annual reports of progress and by immediate notification of adverse events by the PI to the IRB, the ACCTS, and any federal regulatory agency (e.g. FDA) when appropriate or required.

The Rockefeller University Clinical Research Office will conduct spot audits, “for cause” audits, and reviews, upon the request of the investigators.

**Safety review and monitoring:**

All laboratory tests will be reviewed and signed by the investigator on a timely basis. MSKCC, which is a CLEP certified laboratory, will be used. Only lab results obtained from under CLEP certified conditions will be shared with patients.

Adverse events (AEs) are compiled for each patient, for each study, and on a weekly basis in a central book in the lab. Compiled data is verified using source documents. Furthermore, AE’s are reviewed on a monthly basis and tracked. Minutes will be kept of the monthly review.

Study monitoring will occur on a regular basis. Charts will be reviewed for completeness as source documents, e.g. grading and attribution of all AEs, start/stop information for all AEs, confirmation of study eligibility, up-to-date informed consent, submission of all amendments, etc., by the study coordinator. A log will document the occurrence of regular monitoring activities.

The study coordinator, or investigator, manages protocol-specific data on paper forms organized by patient number and/or study. These are kept in a secure, double locked area of the lab. All lab personnel that work with patient data or samples have passed human subject protection courses and will keep data confidential in designated laboratory files. Data are not recorded in computerized spreadsheets, except for final analysis of data. Since Microsoft excel is often used for data analysis, only the primary “sheet” is used and data cannot be copied to another sheet. Data entries are certified against primary source documents in the lab.

**Adverse Events (AEs)**

The Common Toxicity Criteria (CTC) Grading Scale v3.0 (<http://ctep.cancer.gov/forms/CTCAEv3.pdf>), a standard and widely used instrument, will be used to define, grade and attribute adverse events (AEs). Any AEs encountered during the study will be recorded, and AEs will be reported as outlined in the table below.

| **Type of AE** | **Report to:** | **Timeframe for reporting** | **Web Reference** |
| --- | --- | --- | --- |
| All AEs | RU IRB | Annually | <http://clinfo.rockefeller.edu/irb/irb-ind.htm>  Procedures Section 17 |
| Unexpected AEs > grade 2; Serious AEs | RU IRB | Within 2 working days* | <http://clinfo.rockefeller.edu/irb/irb-ind.htm>  Procedures Section 17 |
| Both serious and unexpected AEs | FDA, Sponsor | As soon as possible (phone, fax writing), but within 7 days* | <http://www.accessdata.fda.gov/scripts/cdrh/cfdocs/cfcfr/CFRSearch.cfm?fr=312.32> |

* time since discovery

All AEs will be reported directly to The Rockefeller University IRB and the ACCTS both orally at the annual meetings and in writing as an annual report in the protocol. The annual summary will include:

1-All AEs will be summarized in tabular form; including grade for all AEs, attribution information for grade 3 and 4, and dose reduction information where appropriate.

2-Total enrollment, demographics of enrollment, protocol violations current status of subjects (completed, ongoing, dropout), reasons for attrition, and number of subjects reaching primary endpoints.

3-Available research data, especially any that might provide evidence of early proof or dis-proof of the hypothesis.

Unexpected AEs (of grade 2 or greater severity) and any serious adverse event (SAE) will be reported to the **IRB** within 2 working days of discovery as directed by The Rockefeller University IRB Procedures Manual version date 2/3/07.

Unexpected AEs (of grade 2 or greater severity) and any serious adverse event (SAE) will be reported to the **FDA** and **Sponsor** as soon as possible after discovery by telephone, fax or writing, but within 7 days, and with a full written report within additional 8 calendar days. This conforms to standard good clinical practice (GCP) guidelines (ICH Tripartite Guideline. Clinical Safety Data Management: Definitions and Standards for Expedited Reporting, Part B, no 1)

Any IND Safety Reports received from the Sponsor will be filed with the IRB promptly.

Any pregnancy that occurs during the study, although not itself an SAE, should be recorded as an SAE and expeditiously reported to the Sponsor to facilitate outcome follow-up. Abortion, whether it be accidental, therapeutic, or spontaneous, should be reported as an SAE. Similarly, any congenital anomaly/birth defect in a child born to a subject exposed to the investigational treatment should be reported as an SAE.

A female subject must be instructed to stop taking study drug and immediately inform the investigator if she becomes pregnant during the study. Pregnancies beginning within 90 days after the completion of the last dose of study drug must also be reported to the investigator. The Investigator should counsel the subject, discussing the risks of continuing with the pregnancy and the possible effects on the fetus. Monitoring of the subject should continue until conclusion of the pregnancy. Pregnancy occurring in the partner of a subject participating in the study should also be reported to the investigator and Sponsor.

**15. Procedures to Minimize risks:**

Safety will be assessed through monitoring of all adverse events that occur following the first study drug treatment on Day 0. Subjects will be instructed about possible acute adverse events and first‑dose effects. Patients will be given detailed written instructions (see appendix G). Safety assessments will include routine laboratory tests (hematology, chemistry, urinalysis, and urine pregnancy tests, if appropriate). Periodic complete dermatologic examinations will be performed with careful surveillance for skin cancer and herpetic infections. In addition, a summary will be produced for each of the following:

- Serious adverse events
- Events leading to withdrawal from treatment
- Events judged by the investigator to be related to study drug
- All events by severity
- Acute adverse events
- Infections
- Events potentially indicative of hypersensitivity

Study Medication Accountability

All study drug required for completion of this study will be provided by Genentech. The recipient will acknowledge receipt of the drug by returning the INDRR-1 form indicating shipment content and condition. Damaged supplies will be replaced.

Accurate records of all study drug dispensed from and returned to the study site should be recorded on the Drug Inventory Log.

All partially used or empty containers should be disposed of at the study site according to institutional standard operating procedure. Return unopened, expired, or unused study drug with the Inventory of Returned Clinical Material form as directed by Genentech.

Disclosure of Data

Upon the subject’s permission, medical information may be given to his or her personal physician or other appropriate medical personnel responsible for his or her welfare.

Data generated by this study must be available for inspection upon request by representatives of the U.S. FDA, national and local health authorities, Genentech (and its licensees and joint developers), and the IRB/EC for each study site, if appropriate.

Retention of Records

U.S. FDA regulations (21 CFR §312.62[c]) require that records and documents pertaining to the conduct of this study and the distribution of investigational drug, including CRFs, consent forms, laboratory test results, and medication inventory records, must be retained by the Principal Investigator for 2 years after marketing application approval. If no application is filed, these records must be kept 2 years after the study is discontinued and the U.S. FDA and the applicable national and local health authorities are notified. Genentech will notify the Principal Investigator of these events.

For studies conducted outside the United States under a U.S. IND, the Principal Investigator must comply with U.S. FDA IND regulations and with those of the relevant national and local health authorities.

**16. Potential Benefits:**

For the individual patient, the major benefit that could be derived from this study is the complete clearing of psoriasis, without the need for alternative therapy. Benefits to society include the possibility that the study medication may prove to be more efficacious and have a superior therapeutic index than currently available anti-psoriatic therapies.

**17. Risk to Benefit Ratio -** favors participating in study

**APPENDIX A**

**Psoriasis Area and Severity Index (PASI)**

Evaluator Requirements

 The evaluator must be a dermatologist or an experienced health care provider.

 The evaluator must have attended the Investigator meeting or have been trained by someone who attended the Investigator meeting.

 The same evaluator should determine all PASIs for any individual subject throughout the trial.

A backup evaluator is only allowed in case of emergency or special situation when the designated evaluator is unable to perform the evaluation. The backup evaluator must be a dermatologist or an experienced health care provider and have attended the Investigator meeting or have been trained by someone who attended the Investigator meeting.

General Instructions

1. For each area of the body, rate erythema, scaling, and thickness for the **average** plaque or the overall condition of plaques in that region.

2. Rate plaques as they are actually seen on the day of examination. Do not rate in comparison with baseline condition.

PASI Scoring

PASI scores can range from 0 to 72. Dermatologic disease severity is to be scored as follows:

Body Areas

Four main body areas will be assessed, the head (h), the trunk (t), the upper extremities (u), and the lower extremities (l) corresponding to 10%, 30%, 20%, and 40% of the total body surface area (BSA), respectively.

APPENDIX A (cont’d)

Psoriasis Area and Severity Index (PASI)

The area of psoriatic involvement for each body area (Ah, At, Au, Al) will be assigned a numerical value according to degree of involvement as follows:

0 = no involvement
1 = <10% involvement
2 = 10% to <30% involvement
3 = 30% to <50% involvement
4 = 50% to <70% involvement
5 = 70% to <90% involvement
6 = 90% to 100% involvement

Conventions for estimating BSA include the following:

 Include only currently active disease in affected area:

For small, scattered lesions do not include the skin between the lesions in the estimate;

For a centrally cleared plaque, count only area of inflamed outer ring;

Do not include residual hyperpigmentation, hypopigmentation, pigmented macules, or diffuse slight pink coloration

 Assignments for the following body segments are:

Neck: include with the head
Buttocks: include with the lower extremities
Axillae: include with trunk
Genitals: include with the trunk
Separation of trunk and lower extremities: the inguinal canal separates the trunk and legs anteriorly

Psoriatic Lesion Signs

In addition, the severity of the psoriatic lesions in three main signs—erythema (E), thickness (T), and scaling (S)—will be assessed for each body area according to a scale (0–4) in which 0 represents a complete lack of cutaneous involvement and 4 represents the most severe possible involvement.

